## 1 PROTOCOL SUMMARY

### 1.1 SYNOPSIS

**Title:** Effectiveness and Implementation of a Primary Healthcare Intervention for Screening and Management of Multimorbidity and Frailty among Urban Older Adults: The Multi-FrAME Study

**Design:** Phase 3 cluster randomized, parallel arm, observer-blinded trial.

**Objective:** To assess the effectiveness of the Multi-FrAME intervention package in improving health outcomes for older adults with multimorbidity and frailty.

**Setting:** Urban Primary Healthcare Centres (PHCs) in Bhubaneswar, India.

**Participants:** Older adults (aged 60+) with multimorbidity and frailty (Frailty Index  $\geq 25$ ), without dementia, and not bedridden.

**Intervention:** The Multi-FrAME package, which includes medical management, nutritional support, physiotherapy, physical activity, and psychosocial counselling.

**Comparator:** Standard routine care.

**Primary Outcome:** Improvement in health-related quality of life, measured by EQ-5D-5L index scores.

**Secondary Outcomes:**

- Changes in frailty index scores
- ADL/IADL scores
- Healthcare utilization and expenditure
- Patient satisfaction
- Medication adherence
- Mortality rates

**Data Collection:** Baseline, 6, and 12 months.

**Safety Monitoring:** Regular assessment of adverse events and serious adverse events throughout the study.

**Analysis:** Intention-to-treat analysis, with planned interim analysis after 50% completion of the 12-month follow-up.

**Ethical Considerations:** Approved by the Institutional Human Ethical Committee of ICMR-RMRC Bhubaneswar, adhering to ICMR guidelines [ICMR-RMRC/IHEC-2024/015].

This trial aims to provide insights into effective management strategies for older adults with complex health needs in a primary care setting.

**CTRI Registration: CTRI/2024/09/073487**

## 1.2 SCHEMA

- i. **Enrollment:**
  - a. Screening for eligibility using the MAQ-PC plus tool, frailty index and DART test.
- ii. **Randomization:**
  - a. Clusters (PHCs in Bhubaneswar) randomly assigned to either:
    - i. **Intervention Group:** Multi-FrAME package
    - ii. **Control Group:** Standard routine care
- iii. **Intervention Components (Multi-FrAME):**
  - a. Medical management
  - b. Nutritional support
  - c. Physiotherapy and physical activity
  - d. Psychosocial counseling
- iv. **Data Collection Time Points:**
  - a. Baseline
  - b. Follow-up at 6 months
  - c. Follow-up at 12 months
- v. **Outcome Measures:**
  - a. **Primary:** EQ-5D-5L index scores
  - b. **Secondary:** Frailty index, ADL/IADL scores, healthcare utilization/expenditure, patient satisfaction, medication adherence, mortality
- vi. **Monitoring and Safety:**
  - a. Monthly contact sessions for intervention fidelity and data collection
  - b. Continuous monitoring of AEs and SAEs
  - c. Training of all sites on identifying AE/SAE
  - d. Overview by DSMB
- vii. **Analysis:**
  - a. Intention-to-treat approach

- b. Interim analysis after 50% completion of the 12-month follow-up
- viii. **Completion:**
  - a. Endline assessments at 12 months
  - b. Data analysis and dissemination of findings

### 1.3 SCHEDULE OF ACTIVITIES

| Activity                             | Screening | 0 Month    | 6 Months   | 12 Months  |
|--------------------------------------|-----------|------------|------------|------------|
| Eligibility Assessment               | ✓         |            |            |            |
| Informed Consent                     | ✓         |            |            |            |
| Randomization                        |           | ✓          |            |            |
| Medical Assessment                   |           | ✓          | ✓          | ✓          |
| EQ-5D-5L Quality of Life Assessment  |           | ✓          | ✓          | ✓          |
| Frailty Index Evaluation             |           | ✓          | ✓          | ✓          |
| ADL/IADL Assessment                  |           | ✓          | ✓          | ✓          |
| Healthcare Utilization & Expenditure |           | ✓          | ✓          | ✓          |
| Medication Adherence Monitoring      |           | ✓          | ✓          | ✓          |
| Patient Satisfaction Survey          |           |            | ✓          | ✓          |
| Intervention Delivery (Multi-FrAME)  |           | ✓          | Continuous | Continuous |
| Adverse Event Monitoring             |           | Continuous | Continuous | Continuous |
| Lab Tests & Biomarker Collection     |           | ✓          | ✓          | ✓          |

Interim Analysis

After 50% of 12-months

Final Data Collection & Analysis

✓

## 2 INTRODUCTION

### 2.1 STUDY RATIONALE:

The increasing number of older adults in low- and middle-income countries (LMICs) like India will impose a significant burden on health systems in the future. Complex aging pathways, including multimorbidity, frailty, and other syndromes, contribute to this burden. In India alone, the population aged 60 and above is projected to rise dramatically from 103 million to 319 million by 2050, representing nearly 20% of the total population (United Nations, 2022).

Multimorbidity, defined as the coexistence of two or more chronic conditions, and frailty, characterized by increased vulnerability to stressors due to diminished physiological reserve, are prevalent worldwide. Studies reveal that over 70% of older adults in high-income countries experience multimorbidity, with significant prevalence also observed in LMICs (Barnett et al., 2012; Marengoni et al., 2011).

Frailty is particularly relevant in individuals with multimorbidity, as it often exacerbates health outcomes, including increased risk of hospitalization, disability, and mortality. Identifying and managing frailty in this group is crucial as a public health strategy. Research shows a strong association between multimorbidity and frailty, where frailty significantly worsens the impact of chronic diseases (Fried et al., 2001).

Frailty adversely affects numerous health outcomes, notably reducing patient-reported quality of life (QoL). Frail individuals report lower scores in mental and emotional well-being, impacting their overall life satisfaction (Collard et al., 2012). This highlights the need for interventions that address frailty to improve QoL and health outcomes.

Systematic reviews indicate various intervention types, such as exercise programs, nutrition support, and comprehensive geriatric assessments, can mitigate frailty and enhance QoL and other

patient-reported outcome measures (PROMs). However, the evidence predominantly stems from high-income countries, leaving a gap regarding LMICs (Clegg et al., 2013; Puts et al., 2017).

Further trials are essential, particularly focusing on frailty-related interventions in LMICs where evidence is scarce. In India, there is a dearth of research exploring these interventions. Systematic reviews underscore the urgent need for studies from this region to contribute valuable data (Abizanda et al., 2016; Apóstolo et al., 2018).

This trial intends to address this gap by evaluating a comprehensive intervention targeting multimorbidity and frailty among older adults in urban India. The findings aim to inform policy and practice, ultimately improving healthcare delivery and outcomes for this vulnerable population.

## 2.2 BACKGROUND:

The increasing prevalence of age-related syndromes, such as multimorbidity and frailty, presents significant challenges to global healthcare systems, particularly in low- and middle-income countries (LMICs) like India. As the demographic shifts towards an older population, with projections showing the number of adults aged 60 and above rising to 319 million by 2050 (United Nations, 2022), addressing the complex needs of older adults becomes crucial.

**Multimorbidity** refers to the coexistence of two or more chronic medical conditions within one individual, often leading to complex healthcare needs and management challenges. Globally, more than 70% of older adults experience multimorbidity, which is associated with a higher risk of adverse outcomes including increased healthcare utilization, polypharmacy, and reduced quality of life (Barnett et al., 2012). In India, a significant proportion of the elderly population is affected, highlighting the urgent need for integrated care approaches (Pramesh et al., 2014).

**Frailty**, often coexisting with multimorbidity, is characterized by decreased physiological reserve and increased vulnerability to stressors, leading to adverse health outcomes such as falls, disability, hospitalization, and mortality (Fried et al., 2001). Frailty affects approximately 10% of community-dwelling older adults globally (Collard et al., 2012), and its prevalence is even higher among those with multiple chronic conditions (Chang et al., 2019).

Importantly, frailty profoundly impacts patient-reported outcomes, significantly diminishing quality of life across physical, mental, and social domains (Dent et al., 2016). Frail individuals often

experience lower satisfaction levels and poorer mental health outcomes, underscoring the importance of targeted interventions.

Several intervention strategies have demonstrated potential in mitigating frailty and its effects. Comprehensive geriatric assessments, multidisciplinary care models, and personalized interventions focusing on exercise, nutrition, and social support have shown promise in improving health outcomes for frail older adults (Clegg et al., 2013; Puts et al., 2017). However, most evidence is derived from high-income countries, leaving a substantial gap regarding applicability in LMICs (Hoogendijk et al., 2019).

### **Gaps in Current Evidence**

Systematic reviews consistently point to a lack of research on frailty-related interventions in LMICs. The unique cultural, economic, and healthcare infrastructures in these regions necessitate context-specific studies to develop sustainable and effective models of care (Abizanda et al., 2016; Apóstolo et al., 2018). In India, where health systems already face numerous challenges, research into culturally appropriate and scalable interventions remains crucial. This trial aims to fill this gap by implementing and evaluating a comprehensive intervention for frail older adults with multimorbidity, contributing valuable insights to the global evidence base.

The management of frailty in older adults is multifaceted, involving various intervention strategies that address medical, physical, nutritional, and psychosocial aspects. Evidence from textbooks and systematic reviews highlights the effectiveness of different approaches, often recommending a combination for optimal outcomes.

**Medical Management-** Effective management of existing chronic conditions and medication adherence are crucial in preventing the progression of frailty. Ensuring regular review and optimization of medication regimens can reduce polypharmacy risks, improve health outcomes, and enhance quality of life (Maher et al., 2014). Systematic reviews suggest that medication management, including deprescribing unnecessary medications, significantly impacts frailty levels (Gnjidic et al., 2012).

**Physiotherapy and Physical Activity/Exercise-** Exercise and physiotherapy are fundamental components in managing frailty, with substantial evidence supporting their role in improving muscle strength, balance, and overall physical function. Resistance and aerobic exercises, tailored to

individual capabilities, have been shown to reduce frailty and improve independence in daily activities (de Labra et al., 2015). Comprehensive exercise programs are recommended in geriatric care models (Landi et al., 2018).

**Nutritional Supplementation-** Nutritional interventions, including supplementation with Vitamin D3, iron, folic acid, calcium, and protein, play a vital role in managing frailty. Vitamin D3 supplementation has been linked to improved muscle function and reduced fall risk (Bischoff-Ferrari et al., 2016). Iron and folic acid can address anemia-related fatigue, enhancing energy and activity levels (Fairweather-Tait et al., 2014). Calcium and protein intake are essential for maintaining bone health and muscle mass, crucial in slowing frailty progression (Bauer et al., 2013).

**Psycho-Social Counselling Based Interventions-** Psycho-social interventions are critical in addressing the mental and emotional aspects of frailty. Counseling and support groups improve social connectivity, reduce depression, and enhance coping mechanisms, all contributing to better quality of life (Wuthrich et al., 2015). Cognitive-behavioral therapy has shown benefits in reducing anxiety and improving self-efficacy among older adults (Chodosh et al., 2015).

Despite the available evidence, most studies are from high-income countries, necessitating further trials in LMICs like India. Limited context-specific research exists for these interventions, highlighting an urgent need for studies exploring their applicability in diverse settings (Apóstolo et al., 2018; Hoogendijk et al., 2019).

This trial aims to fill this gap by implementing and evaluating a comprehensive intervention for frail older adults with multimorbidity in an urban Indian setting, providing critical insights for global health policy.

**AHSETS Study:** Our previous work exploring the complex interactions between aging syndromes, including multimorbidity and frailty, within the AHSETS community-based cohort, underscores the need for comprehensive primary care interventions targeting multiple conditions and outcomes. These interventions should transition from disease-specific approaches to patient-centered models that emphasize early identification, integrated care, and coordination among multidisciplinary teams ([name] et al., 2020; [name] et al., 2021). Tailored care can significantly improve health outcomes, reduce costs, and enhance quality of life for older adults ([name] et al., 2020).

Urban primary healthcare services, especially health and wellness centers, are crucial in delivering accessible care to older adults. However, there is limited evidence on the effectiveness of managing multimorbidity and frailty within these settings. Current primary care models often lack the comprehensive, integrated care required by these patients ([name] et al., 2023).

This clinical trial protocol aims to address this gap by developing and evaluating an integrated, multidimensional intervention for older adults with multimorbidity and frailty in urban primary healthcare centers. The focus is on delivering proactive, coordinated care through a patient-centered approach involving multidisciplinary teams, thereby improving management and reducing the burden on healthcare systems in LMICs like India.

## 2.3 RISK BENEFIT ASSESSMENT

### 2.3.1 KNOWN POTENTIAL RISKS:

#### A. Nutritional Supplementation

##### i. Vitamin D3 (Cholecalciferol)

- **Hypercalcemia:** Excessive intake can lead to elevated calcium levels, causing nausea, vomiting, weakness, frequent urination, and kidney damage. Symptoms may appear when serum calcium exceeds 10.5 mg/dL (Jones, 2008).
- **Hypervitaminosis D:** Chronic high doses can result in toxicity, symptoms include confusion, disorientation, and cardiovascular complications (Holick, 2007).
- **Gastrointestinal Disturbances:** Constipation, diarrhea, or abdominal discomfort may occur (Vieth, 1999).

##### ii. Calcium

- **Kidney Stones:** Increased risk of calcium oxalate stones, leading to renal colic (Curhan et al., 1997).

- **Hypercalcemia:** Similar symptoms to Vitamin D3 excess.
- **Gastrointestinal Symptoms:** Bloating, gas, or constipation, especially at high doses (Straub, 2007).

### iii. **Iron**

- **Gastrointestinal Upset:** Nausea, vomiting, diarrhea, and constipation (Haas & Brownlie, 2001).
- **Iron Overload:** Conditions like hemochromatosis can occur with chronic excessive intake, leading to organ damage (Borgna-Pignatti et al., 2010).
- **Staining of Teeth:** Liquid supplements may cause staining (Provan, 1999).

### iv. **Folic Acid**

- **Masking of Vitamin B12 Deficiency:** Can lead to neurological damage if B12 deficiency goes undiagnosed (Chanarin & Metz, 1997).
- **Gastrointestinal Symptoms:** Mild bloating or gas may occur (Tamura & Picciano, 2006).

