#### iii. **Liver and Kidney Function Tests:**

- a. **Outcome Measurement:** Changes in enzyme levels (e.g., ALT, AST) and creatinine (along with eGFR).
  - b. **Justification:** Indicates improvements in organ function.
- iv. **Complete Blood Count (CBC):**
  - a. **Outcome Measurement:** Hemoglobin and hematocrit levels. Along with WBC ratios.
  - b. **Justification:** Indicates overall hematological health and potential for anemia improvement.
- v. **Micronutrient Levels:**
  - a. **Outcome Measurement:** Changes in Vitamin D, iron, and calcium levels.
  - b. **Justification:** Provides insight into nutritional and bone health improvements.
- vi. **Thyroid Function Tests:**
  - a. **Outcome Measurement:** Changes in TSH, T3, and T4 levels. Changes in testosterone, oestrogen and progesterone levels
  - b. **Justification:** Reflects endocrine health and potential metabolic improvements.

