## 6 STUDY INTERVENTION(S) OR EXPERIMENTAL MANIPULATION(S)

### 6.1 STUDY INTERVENTION OVERVIEW

The Multi-FrAME package will be implemented at the cluster level across urban PHCs. It includes comprehensive components tailored for addressing multimorbidity and frailty:

- **Medical Management:** Regular review and optimization of medication regimens, as well as tools to improve medication adherence.
- **Nutritional Support:** Education on balanced diets and supplementation with Vitamin D3, iron, folic acid, calcium, and protein as needed.
- **Physiotherapy and Physical Activity:** Customized exercise programs focusing on resistance and aerobic activities.
- **Psychosocial Support:** Individual and group sessions to support mental health and enhance social connections. Health promotion materials provided for self-help.

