| Medical Management                  | Medication review and optimization; Diary for improving adherence and compliance                                                                                         | Monthly, with diary data being updated daily                                                                                                                                                                                 | In-person at PHC                            | Self-care, with caregiver assistance if needed |
| Nutritional Support                 | Vitamin D3, iron, folic acid, calcium, and protein supplements                                                                                                           | Doses are subject to the results of participants' biochemical tests for the respective nutrients. These doses will be monitored and modified as necessary to maintain nutrient levels within the biological reference range. | Oral supplementation                        | Self-care                                      |
| Physiotherapy and Physical Activity | Customized exercise program                                                                                                                                              | Monthly sessions, with daily exercises                                                                                                                                                                                       | In-person sessions and home-based exercises | Self-care, with caregiver support for safety   |
| Psychosocial Support                | Individual and group therapy sessions (Including therapeutic games, storytelling, friendship enrichment program), health promotion through the health diary IEC material | Breathing exercise and Meditation on daily basis, Psychological Counselling as per the patient's requirement, and Group sessions once in 2-3 month                                                                           | In-person or via tele-health                | Self-care                                      |

Details of the intervention are provided as an additional file.

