## 9.2 SAFETY ASSESSMENTS

- **Adverse Events:**
  - **Definition:** Any undesirable experience associated with the use of the intervention.
  - **Assessment Frequency:** Continuous monitoring with mandatory reporting within 24 hours of occurrence.

- **Severity Classification:** Mild, Moderate, Severe based on impact on daily activities.
- **Serious Adverse Events:**
  - **Definition:** Events resulting in death, hospitalization, disability, or jeopardizing participant health.
  - **Reporting:** Immediate notification to Principal Investigator and ethics board, with documentation filed timely.
- **Vital Signs and Routine Checks:**
  - **Parameters:** Blood pressure, heart rate, weight, and BMI.
  - **Frequency:** Monthly during contact sessions.
- **Lab Tests:** (also as outcomes as described above in section 3.2)
  - **Assessment Schedule:** 0, 6, and 12 months.
  - **Tests Included:** (detailed as endpoints in section 3.2)
    - **Biochemical Metrics:** Blood glucose, lipid profile, liver function tests, kidney function tests.
    - **Hematological Metrics:** Complete blood count, hemoglobin levels.
    - **Micronutrient Profiles:** Levels of Vitamin D, iron, and calcium.
    - **Hormonal Profiles:** Thyroid function tests and other relevant hormone levels.

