## 10 ADVERSE EVENTS AND SERIOUS ADVERSE EVENTS

### 10.1 DEFINITION OF ADVERSE EVENTS (AEs)

An adverse event (AE) is any undesirable medical occurrence in a trial participant that may present during the trial, whether related to the intervention or not. This includes any new symptoms or worsening of pre-existing conditions.

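### The protocol names masked vitamin B12 deficiency as a folic acid risk, but no laboratory panel in its body lists B12, so the deficiency would go unseen until it became a clinical event

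*Protocol*

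**What the plan says.** Section 2.3.1, under nutritional supplementation, item iv, gives masking of B12 deficiency as a known risk of folic acid: "Can lead to neurological damage if B12 deficiency goes undiagnosed". B12 is mentioned nowhere else in the protocol.

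Folic acid belongs to the package. Section 6.1 describes "supplementation with Vitamin D3, iron, folic acid, calcium, and protein as needed", and the table in 6.2 adds: "Doses are subject to the results of participants' biochemical tests for the respective nutrients".

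The laboratory content is set out twice. In section 3.3, item v (Micronutrient Levels), the outcome is "Changes in Vitamin D, iron, and calcium levels". In section 9.2 (Safety Assessments) the micronutrient profile is "Levels of Vitamin D, iron, and calcium". The blood count in 3.3 is specified as "Hemoglobin and hematocrit levels. Along with WBC ratios". The only open-ended laboratory entry in 9.2 is "Thyroid function tests and other relevant hormone levels". The laboratory tests are scheduled at 0, 6 and 12 months (1.3 and 9.2).

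**The concern.** By the protocol's own account, the harm depends on the deficiency going undiagnosed. A plan that names such a risk, supplies the supplement that carries it and draws blood three times would be expected to include the measurement that makes the diagnosis. Without that value, the staff who must look for contraindications to each component at enrolment (2.3.3 B.ii) have no listed test for this one. The panel that judges whether an event is related to the intervention (10.5) would have no scheduled B12 result to consult. The closing risk and benefit report (2.3.3 C.iv) could describe neurological events but could not tie them to this mechanism or rule it out.

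This is a matter of participant safety and of interpreting safety data. It does not touch the primary endpoint, the sample size or any error rate.

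**Working it through.** No figure needs to be reproduced. The check is a comparison of lists.

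**Step 1: risks against analytes.** Section 2.3.1 gives risks for four supplements. Set against the laboratory lists in 3.3 and 9.2:

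| Supplement | Main biochemical risk in 2.3.1 | Matching analyte in 3.3 / 9.2 |
|---|---|---|
| Vitamin D3 | Hypercalcaemia, vitamin D toxicity | Vitamin D, calcium |
| Calcium | Hypercalcaemia | Calcium |
| Iron | Iron overload | Iron |
| Folic acid | Masked B12 deficiency | None |

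Three of the four have a named analyte. Folic acid does not.

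**Step 2: could another panel supply B12?** Section 3.3 has six items: glucose, lipids, liver and kidney function, blood count, micronutrients, and thyroid with sex hormones. Section 9.2 groups the tests under four headings: biochemical, haematological, micronutrient and hormonal. B12 is named in 0 of the 6 items and under 0 of the 4 headings. The open-ended wording in 9.2 extends to hormones only. The exploratory analyses (12.4.10) allow for further laboratory parameters but name none. The exclusion criteria (5.2) do not mention B12.

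**Step 3: does the blood count stand in for it?** It is specified as haemoglobin, haematocrit and white cell ratios, none of which is a B12 measurement. The protocol does not explain how the masking works or which finding is masked, so its text gives no ground for treating the count as a substitute.

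**Step 4: the dosing basis.** Section 6.2 makes supplement doses depend on tests for the nutrients concerned. Of the four micronutrients supplied, vitamin D, iron and calcium appear in the panels. Folate appears in neither. For folic acid, the dosing statement therefore refers to a test that the laboratory schedule does not list.

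**Step 5: what would still be recorded.** Section 10.1 defines adverse events irrespective of relatedness and adds: "This includes any new symptoms or worsening of pre-existing conditions". They are assessed continuously and at monthly contacts (10.4), classified for relatedness by a panel (10.5) and compared between groups (12.4.4). Neurological symptoms would enter the data by this route. The listed tests would give neither sight of the deficiency before symptoms nor a laboratory basis for attributing the symptoms to it.

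**Extent.** The gap holds at all 3 scheduled laboratory time points. The number of participants concerned cannot be derived: the protocol states neither how many will receive folic acid nor how common B12 deficiency is in this population.

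**The case against.** The strongest reply is that adverse event reporting already covers the harm. The harm named is neurological damage, and the route in step 5 would record it. This stands. A reader might infer from the missing assay that the safety data are blind to the harm, or that the comparison in 12.4.4 would look the same whether or not it occurred. The protocol does not support either reading. The reply does not remove the rest: event reporting acts once symptoms appear, whereas 2.3.1 places the danger at the undiagnosed stage, and it leaves the cause open. Two features make attribution harder. Section 9.2 defines adverse events more narrowly than 10.1, as experiences associated with the intervention. The frailty index (9.1) also counts functional and cognitive deficits, so such symptoms could be read as progression of frailty.

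Second, a list of risks does not promise a laboratory test for each. That is fair: musculoskeletal injury and emotional distress have no assay and need none. Nor does 2.3.3 say that contraindications must be found by blood test; it also calls for medical history and current medications. But this risk is biochemical, and the protocol itself makes its harm turn on diagnosis.

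Third, the laboratory report forms, intervention details and operating manual are annexures (section 17) that are not available. A B12 assay may be specified there. This stands and limits the finding to the protocol body.

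Fourth, supplementation is given as needed. A reader might picture every intervention participant taking folic acid for 12 months, but the protocol does not say so.

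**Conclusion.** The point holds in a limited form. The protocol body lists masked B12 deficiency as a folic acid risk and supplies folic acid, but names B12 in no laboratory panel at any of the three time points. On that text, a masked deficiency would first be seen as a clinical adverse event, and the listed tests could not establish its cause. The basis given for folic acid doses also refers to a nutrient test that is missing from both panels.

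The conclusion rests on one assumption: that the unavailable annexures do not already specify the assay. It does not extend to saying that the trial cannot observe the harm, and no estimate of the number of participants at risk is possible from the documents. It is a modest, inexpensive safety improvement with no bearing on the efficacy analysis.

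**What to change.** Reconcile sections 2.3.1 (folic acid), 2.3.3 B.ii, 3.3 item v, 6.2 and 9.2:

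- Add B12 to the micronutrient lists in 3.3 and 9.2, run on the blood already drawn at 0, 6 and 12 months. If the laboratory forms or manual already contain the assay, a cross-reference in those sections is enough.
- Bring the dosing statement in 6.2 and the panels into agreement on folate, so that the test relied on for folic acid is identifiable.
- While editing 9.2, correct its pointer for the laboratory tests: it refers to section 3.2, but they are set out in 3.3.

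How a B12 or folate result affects supplementation is for the investigators to set. Merely declaring the risk unmonitored would be honest but would leave the deficiency unseen.

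The cost of adding B12 is one analyte on existing samples, with a small reagent cost, no extra visit or procedure, and a line each in 3.3 and 9.2. If the annexures already cover it, the cost is one sentence.
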